## Abstract

**Background:**

Cognitive impairment (CI) affects a significant proportion of people with Multiple Sclerosis (PwMS), even in the early stages of the disease, increasing fatigue perception and reducing quality of life. Various restorative interventions have been tested to mitigate CI, but their efficacy remains limited. Transcranial direct current stimulation (tDCS) has emerged as a promising add-on to conventional rehabilitation in several neurological conditions, including MS. Similarly, novel technologies such as exergames are gaining attention as supportive tools in the rehabilitation of PwMS. These approaches can be combined within integrated protocols to maximize therapeutic benefits on CI. However, robust evidence of efficacy is still lacking, and only one case report has been published to date.

**Aims:**

The primary aim is to investigate the potential benefits of combining anodal tDCS (A-tDCS) with exergame-based training in the rehabilitation of CI in PwMS. The secondary aim is to assess whether the proposed protocol can provide sustained benefits over time.

**Methods:**

80 PwMS with CI will be consecutively enrolled and evaluated through a comprehensive neuropsychological battery. 40 participants will be randomized to the experimental group (EG) and 40 to the control group (CG). All participants will undergo 10 sessions of exergame-based rehabilitation. In addition, the EG will receive concurrent A-tDCS over the left dorsolateral prefrontal cortex, whereas the CG will receive sham stimulation. Assessments will be conducted at baseline, post-treatment, and at one and six months follow-up.

**Discussion:**

We hypothesize cognitive improvements in both groups due to exergame training. However, we expect greater improvements in the EG compared with the CG. Furthermore, we hypothesize that the beneficial effects in the EG will be sustained over time.

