### Outcome measures

Cognitive status will be assessed using the Brief International Cognitive Assessment for MS (BICAMS) and the Paced Auditory Serial Addition Test (PASAT) with 3- and 2-second intervals. The BICAMS battery includes the Symbol Digit Modalities Test (SDMT), the California Verbal Learning Test, 2nd edition (CVLT-II), and the Brief Visuospatial Memory Test-Revised (BVMT-R). All instruments are widely used in cognitive assessment of PwMS. Patients scoring below the 5th percentile of age-, sex-, and education-adjusted norms in at least two of these tests will be eligible. Additional secondary outcomes will include self-reported measures of mood, fatigue, and quality of life: Multiple Sclerosis Quality of Life (MSQoL) [18], Beck Depression Inventory (BDI) [19], and Fatigue Severity Scale (FSS).

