### Timeline

Outcome measures will be administered at baseline, after the 10 treatment sessions, and at 1-month and 6-month follow-ups. The study duration is estimated at 2 years (Fig 1).

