## Discussion

This project is designed to explore the synergistic effect of A-tDCS and VR-based cognitive rehabilitation in PwMS. By combining two non-conventional restorative approaches, we aim not only to improve cognitive function but also to determine whether the benefits can be sustained over time.

Previous studies have identified key brain regions implicated in attention, information processing and executive function, such as the left DLPFC, cingulate cortices, cerebellum, and parietal areas [1,25]. Our results may contribute to refining this knowledge, clarifying the neural mechanisms underlying CI in MS, and possibly pointing to new therapeutic targets.

Beyond mechanistic insights, integrating A-tDCS with exergames training may promote greater patient engagement, enhancing adherence to cognitive rehabilitation programs. Improved compliance is expected to translate into more durable rehabilitative outcomes and a tangible impact on quality of life.

We anticipate that the combined, simultaneous (on-line) use of A-tDCS and exergames will outperform VR alone (with sham stimulation) in both efficacy and persistence of effects. If confirmed, these findings would strengthen the rationale for implementing integrated neurotechnological protocols in MS rehabilitation, providing protocols that can be translated into everyday rehabilitation settings.

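### Both arms get exergames, so the trial can show only the add-on effect of A-tDCS; change over time is not evidence for exergames, and synergy cannot be examined

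*Protocol article*

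**What the plan says.** **Design.** The Abstract's Methods give every patient the same training: "All participants will undergo 10 sessions of exergame-based rehabilitation". The only planned difference is that "the EG will receive concurrent A-tDCS over the left dorsolateral prefrontal cortex, whereas the CG will receive sham stimulation". No arm goes without exergames, and no arm has stimulation without exergames.

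**Expectations.** The Abstract's Discussion says "We hypothesize cognitive improvements in both groups due to exergame training", and then expects larger gains in the experimental group (EG) than in the control group (CG). The main Discussion opens with "This project is designed to explore the synergistic effect of A-tDCS and VR-based cognitive rehabilitation in PwMS". It later states a different contrast, that the combination "will outperform VR alone (with sham stimulation) in both efficacy and persistence of effects".

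**Entry and testing.** Outcome measures sets the entry rule: "Patients scoring below the 5th percentile of age-, sex-, and education-adjusted norms in at least two of these tests will be eligible". The tests meant are BICAMS (SDMT, CVLT-II, BVMT-R) and the PASAT at 3 and 2 seconds, which also supply the cognitive outcomes. Timeline has four administrations: "Outcome measures will be administered at baseline, after the 10 treatment sessions, and at 1-month and 6-month follow-ups".

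**Analysis.** Statistical analysis and sample size plans a repeated measures ANOVA of SDMT and PASAT with treatment, time and interaction terms. Sample sizes were calculated for the between, within and interaction effects, and the largest was kept. Paired t-tests follow if differences appear.

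**The concern.** Attributing improvement in both arms to exergames is a causal statement about change within arms, and nothing in the trial shows what would have happened without exergames. Synergy means that the joint effect exceeds the sum of the separate effects, so it requires the effect of stimulation without exergames, which is not observed.

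The analysis makes this more than loose wording. It tests a time effect, sizes the trial for a within effect among others, and allows paired tests. A reader who has met the Abstract's expectation will naturally take a significant time effect as its confirmation. That effect is biased upward, because patients are chosen for low scores on the battery on which they are then followed, and they sit it four times.

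At stake are two inferences that no data from this trial could support. The comparison of EG with CG is not at stake.

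**Working it through.** **1. The plan's own figure.** Inputs from Statistical analysis and sample size: power 0.80, significance level 0.05, δ = 0.35, 33 per group for the between effect on PASAT. Reading δ as a between-effect size f, the noncentrality is λ = 66 × 0.35² = 8.085. The noncentral F test on 1 and 64 degrees of freedom then has power 0.7997, so 33 per group reproduces. The between effect, not the time effect, drives the size.

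**2. What the arms identify.** Write mean change as μ(exergames, stimulation), with 1 = given and 0 = not given.

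- EG estimates μ(1,1); CG estimates μ(1,0).
- Add-on effect = μ(1,1) − μ(1,0). Both terms are observed.
- Exergame effect = μ(1,0) − μ(0,0). The second term is not observed.
- Synergy = [μ(1,1) − μ(1,0)] − [μ(0,1) − μ(0,0)]. The second bracket is not observed.

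Suppose EG exceeds CG by D. If stimulation alone is also worth D, synergy is D − D = 0. If stimulation alone is worth nothing, synergy is D − 0 = D. The trial's data are identical in both cases. A larger sample does not help.

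**3. What the time effect contains.** Change from baseline is the sum of exergame effect, practice, sham response (or stimulation effect in EG), disease course and regression to the mean. Only the sum is estimated.

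**4. Size of regression to the mean alone.** The document gives no reliabilities or correlations, so these are assumptions: retest reliability 0.7, 0.8 or 0.9; inter-test correlation 0.4 or 0.6 (higher between the two PASAT versions); source mean 0, −0.5 or −1 SD against norms; the qualifying assessment is also the baseline. Simulation used five normal scores, selection when at least two fall below the 5th percentile, a retest with the same true scores, and no treatment or practice effect. The gain is divided by the SD of change to give d_z. The chance of significance is that of a two-sided paired t-test with noncentrality d_z × √n.

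| Scenario (source mean, reliability, correlation) | Gain SDMT / PASAT-3 (SD) | d_z SDMT / PASAT-3 |
|---|---|---|
| 0, 0.7, 0.4 | 0.14 / 0.17 | 0.18 / 0.22 |
| 0, 0.8, 0.6 | 0.08 / 0.10 | 0.12 / 0.16 |
| −0.5, 0.8, 0.4 | 0.07 / 0.09 | 0.11 / 0.14 |
| −1, 0.9, 0.6 | 0.02 / 0.03 | 0.05 / 0.06 |

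The first and last rows are the extremes of the 18 combinations. In the first, PASAT-3 has noncentrality 0.22 × √33 = 1.26 per arm and 0.22 × √66 = 1.79 pooled, so it is significant in about 23% and 41–42% of trials (the last point varies between simulation runs). In the last, the figures are about 6% and 7%. The gain is positive in every combination.

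**The case against.** The strongest reply is that this is a matter of wording. The formal aims concern the combination and its durability, not exergames alone. Time is an ordinary term in a repeated measures ANOVA, and the statistical section attributes it to nothing. Synergy is something to explore, mentioned in a narrative discussion, and no test of it is specified. The correct contrast, against VR with sham, is already in the same section. All of this is accurate, and it limits the point to two statements and the reading of one model term. It does not rescue them: the arms carry no information on synergy, whether it is explored or tested, and an analysis plan cannot supply missing arms.

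Three stronger readings are tempting, and the document does not support them.

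- *A significant time effect is almost certain without any training effect.* For one test that itself met the criterion, in a source population with the norm mean, expected regression is (1 − r) × 2.063 = 0.62, 0.41 or 0.21 SD for r = 0.7, 0.8 or 0.9. But eligibility needs any two of the tests, so many patients will not have qualified on SDMT or on a given PASAT version, and low scores on several correlated tests point to a truly low level. Averaged over enrolled patients, the figure is 0.02–0.17 SD. Practice could raise it a good deal, but the document gives no figure for practice.
- *The plan rests a confirmatory conclusion on the time effect.* It nowhere says so.
- *The trial's main result is compromised.* Regression to the mean and practice act equally on both arms in expectation, so the randomised comparison stands.

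**Conclusion.** The point holds in limited form. That exergame efficacy and synergy cannot be identified follows from the two arms alone and needs no numerical assumption.

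The upward bias in the time effect is modest from selection alone: about 0.02–0.17 SD on SDMT or PASAT. This gives a significant pre–post test in about 6–23% of trials per arm at n = 33 and about 7–41% pooled at n = 66, against a nominal 5%. These figures rest on the assumed reliabilities, correlations and source means, and on the qualifying scores serving as baseline. A separate baseline after screening would shrink them, and practice would add to them. The EG versus CG comparison, the formal aims and the 33 per group are untouched.

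**What to change.** - In Statistical analysis and sample size, state that efficacy conclusions rest only on the randomised contrast, that is, the treatment and time-by-treatment terms. Persistence at 1 and 6 months should likewise be judged by the difference between arms.
- State there that the time effect and any within-arm pre–post comparisons are descriptive and are not evidence that exergames work.
- In the Abstract's Discussion, delete the attribution of improvement to exergame training.
- In the main Discussion, replace *synergistic effect* with *add-on effect*, which matches that section's own contrast with VR plus sham.

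No patients, visits or arms are added and the sample size stays as it is. The cost is rewording and giving up a claim that the design cannot support.

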**Clinical trials registration:**

ClinicalTrials.gov, Identifier: NCT07114809 (Date: August 8th, 2025)

## Introduction

Cognitive impairment (CI) is one of the many symptoms that can affect individuals with Multiple Sclerosis (MS), potentially compromising activities of daily living (ADLs) and social functioning. Many papers investigate this aspect of the disease, documenting that cognitive dysfunction occurs in a high percentage of cases, ranging from 40% to 82%. The possible therapeutic approaches are mostly neuropsychological rehabilitation treatment, since pharmacological and immunosuppressive therapies did not show significant results [1]. Rehabilitation aims to increase the patient’s awareness of their own CI and create mechanisms for them to manage with CI in daily life, but especially to reduce cognitive deficits through cognitive retraining. Before undergoing the rehabilitation treatment, it is very important to accurately test the cognitive sphere to clearly identify if the impairment is in attention, working memory, information processing speed, visuospatial or executive deficits [2]. In recent years, transcranial direct current stimulation (tDCS) has emerged as a non-conventional tool in restorative neurology due to its ability in enhancing the efficacy of conventional therapeutic interventions. TDCS treatment consists of applying a direct current flow of low intensity (1–2 mA) over the scalp to modulate cortical excitability, by facilitating or inhibiting ongoing neuronal processes. Particularly, the anodal stimulation (A-tDCS) promotes mechanisms that underlie long-term potentiation and triggers widespread cortical activation [3]. The procedure is well-tolerated, with no evidence of risk for serious adverse effects and no associated risk of seizures [4]. TDCS has been reported to exert beneficial effects on pain, fatigue, tactile perception, cognition, attention and executive function [4–9]. Mattioli and coworkers [8] observed a beneficial effect of A-tDCS over the DLPFC on some cognitive domains. Grigorescu [10], on the other hand, found that bifrontal tDCS over the prefrontal cortex (PFC) did not lead to any effect on cognitive measures. These somehow conflicting studies show that further research is needed to better understand the potential role of tDCS in improving the cognitive performance in people with multiple sclerosis (PwMS) and which brain areas are the ideal target for stimulation.

Other novel technologies, such as Virtual Reality (VR) and exergames, are emerging as a reinforcing tool to the rehabilitative treatment of PwMS [11,12]. Systematic reviews on VR in rehabilitation across different neurological conditions, such as MS [13], suggest that VR serves as a motivating and engaging method of rehabilitation, thus potentially increasing therapeutic compliance. VR is well-suited to the use of exergames, which are games designed for a purpose beyond simply entertainment. Exergames have demonstrated their utility for both cognitive and motor rehabilitation, also in PwMS [14] as they exert beneficial effects on attention, visuo-spatial function, executive control, strategic planning, and processing speed. Both these novel techniques, tDCS and VR, can be put together in protocols aimed at achieving a better therapeutic benefit across different neurological diseases. Although evidence is still limited, converging findings suggest potential therapeutic benefits of their combined use [15].

In MS, however, literature still lacks strong evidence of efficacy. Therefore, randomized, controlled trials on an adequate number of PwMS are warranted. A preliminary description of the study concept was included in the doctoral dissertation of [name] (University of Genoa, 2023). However, the current manuscript reports the finalized protocol, which was subsequently revised, approved by the Regional Ethics Committee (CET Liguria, No. 447/2023 – DB id 13376), and registered at ClinicalTrials.gov (NCT07114809) [26]. This prompted us to implement a cognitive rehabilitation project in PwMS by combining A-tDCS with exergames. The primary aim is to investigate the potential benefits of combining A-tDCS with exergame-based training in the rehabilitation of CI in PwMS. The secondary aim is to assess whether the proposed protocol can provide sustained benefits over time.

## Materials and methods

### Study design

We planned a double-blind, randomized, prospective, controlled study. A total of 80 MS patients with CI will be recruited.

### Participants

Participants will be recruited from the outpatient services of the Department of Neurology, ASL3 Genoa, the AISM Liguria Rehabilitation Service, and the Neurorehabilitation Unit of IRCCS Ospedale Policlinico San Martino, Genoa. Inclusion criteria are: (1) diagnosis of MS according to McDonald’s criteria [16]; (2) age between 18 and 60 years (to minimize potential age-related CI); and (3) Expanded Disability Status Scale (EDSS) score ≤7.5 [17]. Exclusion criteria include major psychiatric disorders, epilepsy, previous brain surgery, MS relapse requiring steroid therapy within the past two months, and bilateral visual acuity <6/10.

### Outcome measures

Cognitive status will be assessed using the Brief International Cognitive Assessment for MS (BICAMS) and the Paced Auditory Serial Addition Test (PASAT) with 3- and 2-second intervals. The BICAMS battery includes the Symbol Digit Modalities Test (SDMT), the California Verbal Learning Test, 2nd edition (CVLT-II), and the Brief Visuospatial Memory Test-Revised (BVMT-R). All instruments are widely used in cognitive assessment of PwMS. Patients scoring below the 5th percentile of age-, sex-, and education-adjusted norms in at least two of these tests will be eligible. Additional secondary outcomes will include self-reported measures of mood, fatigue, and quality of life: Multiple Sclerosis Quality of Life (MSQoL) [18], Beck Depression Inventory (BDI) [19], and Fatigue Severity Scale (FSS).

### Methodology

Participants will be randomized into two groups: 40 in the experimental group (EG) and 40 in the control group (CG), matched for demographic characteristics (sex, age), EDSS score, and disease duration. All participants will undergo cognitive training using the Neurotablet system, a virtual-reality–based platform incorporating exergames for motor and cognitive rehabilitation. The system includes exercises with adjustable difficulty levels, enabling tailored treatment plans based on individual disability. The rehabilitation program will consist of 10 sessions (1 hour each), delivered 5 days per week for 2 consecutive weeks.

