### Statistical analysis and sample size

Descriptive characteristics of the included patients will be presented as mean ± standard deviation (SD) or median and interquartile range (IQR) for continuous variables and as absolute frequencies and percentages for categorical variables. Baseline characteristics of the patients will be also shown splitting the patients into the two groups of treatments and comparisons will be performed using Chi-squared test of Fisher’s exact test (for categorical variables) and Mann-Whitney U test or t-test (for continuous variables). Results of the SDMT and PASAT tests will be presented over time as Mean ± SD by showing separately the two groups of treatment. The repeated measures ANOVA will be used to assess the effect of treatment, the effect of time, and the interaction effect between time and treatment on the performance of the SDMT and PASAT tests. The sample size was calculated fixing a power of 0.80 and a significance level of 0.05 and we calculated the sample sizes required for between effect, for within effect and for the between–within interaction effects for both the neuropsychological tests, planning of picking as our final sample size the largest one. To calculate sample sizes, means of measurements over time and covariance matrix for the repeated measures were defined for the SDMT and PASAT tests based on clinical expectations and on previous findings [24]. The largest sample size was the one required for the between effect in the analysis of PASAT test, leading to a sample size of 33 patients in each group to detect the treatment effect of magnitude δ = 0.35. This sample size is even more satisfactory for the SDMT test, where a smaller sample size was required. However, assuming a drop-out rate of 20%, we finally need to enroll in 80 subjects with 40 patients per treatment group. After performing the repeated measures ANOVA, in case of presence of differences, we also plan to compare means using paired t-test, adequately adjusting for multiple testing. In case of missing data over follow-up, a multiple imputation by chained equations approach will be used with 10 imputations. Additionally, we will also perform the same analyses, using complete data to check the robustness of the results. A p value less than 0.05 will be considered significant. All the analyses will be conducted with the Statistical Software Stata version 16.0 (Stata Corporation, College Station, TX, USA). Randomization will be performed using computer-generated random numbers.

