
### Oversight and monitoring

The IRCCS Ospedale Policlinico San Martino, Genoa, will act as coordinating center, responsible for trial oversight, central randomization, data management, monitoring, and communications with the ethics committee and trial registry. Participants will be recruited at three sites (ASL3 Neurology Department, AISM Liguria Rehabilitation Service, and IRCCS Policlinico San Martino). Each site will have a principal investigator responsible for local conduct. A Steering Committee (PI, site PIs, statistician, data manager) will oversee scientific and operational aspects, including protocol amendments, recruitment, adherence, and data quality. Data will be entered into password-protected eCRFs stored on a secure institutional server, with anonymization, restricted access, and regular back-ups. Given the low-risk nature of the trial, no Data Monitoring Committee is planned; safety will be overseen by the PI and site PIs and reported to the ethics committee.

Participants will be withdrawn in case of intolerable adverse events, clinical worsening requiring treatment changes, participant request, or investigator decision for safety. Stimulation parameters will not be modified during the trial. Adherence will be promoted through flexible scheduling, continuous support, and the engaging use of exergames.

Unblinding is not anticipated but may be authorized by the PI in exceptional safety-related circumstances. In case of discontinuation or deviation, all scheduled outcome data (clinical, neuropsychological, and patient-reported) will continue to be collected and included in intention-to-treat analyses.

All adverse events (AEs), whether solicited or spontaneous, will be documented; minor AEs will be managed immediately, while serious/unexpected AEs will be reported promptly to the PI and ethics committee. Any important protocol modifications will be submitted for ethics approval and updated in the trial registry.

Personal data will be collected only for study purposes, stored securely, and anonymized for analysis/publication. The final dataset will be accessible to the PI and study team only; the sponsor has no restrictions on access. No specific ancillary or post-trial care is planned; clinical needs will be managed as per standard practice. Given the minimal risk profile of tDCS and exergames, no specific compensation beyond national regulations is planned.

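### The arms are described as matched on sex, age, EDSS and disease duration, but no stated method produces this and the stated model leaves the four factors out, at a cost in precision rather than validity.

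*Protocol article*

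**What the plan says.** The Methodology section promises two randomised groups, "40 in the experimental group (EG) and 40 in the control group (CG), matched for demographic characteristics (sex, age), EDSS score, and disease duration".

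The mechanism appears at the end of Statistical analysis and sample size: "Randomization will be performed using computer-generated random numbers". Oversight and monitoring adds that the coordinating centre is "responsible for trial oversight, central randomization, data management, monitoring", and that "Participants will be recruited at three sites". No section names blocking, stratification or minimisation.

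The analysis is set out in Statistical analysis and sample size: "The repeated measures ANOVA will be used to assess the effect of treatment, the effect of time, and the interaction effect between time and treatment". The four factors are not named as model terms. Baseline characteristics are described and compared by arm, but the section attaches no adjustment to that comparison.

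The same section gives the sizing: "The sample size was calculated fixing a power of 0.80 and a significance level of 0.05". The largest requirement came from the between effect for PASAT, "leading to a sample size of 33 patients in each group to detect the treatment effect of magnitude δ = 0.35". This was raised to 40 per arm for an assumed 20% drop-out.

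**The concern.** The article claims a property of the groups that its stated mechanism does not supply. A list of random numbers can be arranged to give exactly 40 per arm, but that does not balance the arms on four patient characteristics, three of them continuous or near-continuous. Either some balancing method exists and is not named, or 'matched' describes a hope.

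The analysis is affected under both readings. By listing these factors the sponsor treats them as relevant to outcome, yet the stated model does not use them. If allocation does not balance them, their contribution stays in the error term. If allocation does balance them, the usual unadjusted standard error is too large for the design. What is at stake is precision on the effect that fixed the sample size, and whether readers can tell how patients were allocated.

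**Working it through.** **Inputs from the protocol article.** Power 0.80, significance level 0.05, effect size δ = 0.35 and 33 per arm for the PASAT between effect; 40 per arm enrolled; 20% drop-out (all in Statistical analysis and sample size). Four factors named (Methodology); three sites (Oversight and monitoring).

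**Assumption.** R² is the share of between-patient variance in the outcome that the four factors explain. The document gives no value, so 0.1, 0.2 and 0.3 are shown.

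**Step 1. Reproduce the plan's figure.** Read δ as the between-effect size in an F test with 1 and N − 2 degrees of freedom and noncentrality λ = N × δ². With N = 66, λ = 66 × 0.35² = 8.085 and power is 0.7997. As a cross-check, δ = 0.35 with two equal arms is a standardised difference of 0.70, and 2 × (1.96 + 0.8416)² / 0.70² = 32.04, rounded up to 33. The plan's 33 is reproduced.

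There is no slack. After 20% drop-out from 40, 32 remain per arm (N = 64) and power is 0.787.

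**Step 2. Does a fixed 40/40 random split match the arms?** Fix the arms at 40 each, with no balancing on the factors. The standardised difference on one factor has standard error √(2/40) = 0.224.
- One factor: P(difference above 0.25 SD) = 2 × [1 − Φ(0.25/0.224)] ≈ 0.26.
- At least one of four, if independent: 1 − (1 − 0.26)⁴ ≈ 0.70.
- A simulation of 20,000 runs per setting, with an assumed 70/30 sex split, gave 0.72 with independent factors and 0.69 with correlations of 0.4 among age, EDSS and disease duration.

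So arm sizes can be exact while the arms are not matched. This measures what 'matched' would have to deliver. It does not measure bias.

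**Step 3. No balancing on the factors: what adjustment gains.** Adjustment divides the error variance by 1/(1 − R²), so λ becomes 8.085/(1 − R²). Four covariates cost 4 degrees of freedom: 64 − 4 = 60.

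| R² | λ | Power at 33 per arm |
|---|---|---|
| 0 (covariates explain nothing) | 8.085 | 0.799 |
| 0.1 | 8.98 | 0.839 |
| 0.2 | 10.11 | 0.879 |
| 0.3 | 11.55 | 0.917 |

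The R² = 0 row is the worst case: power falls from 0.7997 to 0.799. Adding three sites costs 2 more degrees of freedom (58 left) and changes no entry by more than 0.001.

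**Step 4. Balancing on the factors, then left out of the model.** The estimate varies less than its reported standard error implies. The test statistic then has variance of about 1 − R² under the null, so type I error = 2 × [1 − Φ(1.96/√(1 − R²))].

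| R² | 1.96/√(1 − R²) | True type I error | Unadjusted power, normal approximation |
|---|---|---|---|
| 0.1 | 2.066 | 0.039 | 0.82 |
| 0.2 | 2.191 | 0.028 | 0.84 |
| 0.3 | 2.343 | 0.019 | 0.85 |

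Power here is 1 − Φ[(1.96 − √66 × 0.35)/√(1 − R²)], which gives 0.81 at R² = 0. Balancing therefore recovers part of the power, and adjustment (0.84, 0.88, 0.92) recovers the rest and brings the type I error back to 0.05.

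**Step 5. Which effect is concerned.** Steps 3 and 4 apply to the between effect. In the time-by-treatment test each patient is compared with his or her own other visits, so a stable factor acting equally at every visit does not enter that error term.

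**The case against.** Computer-generated random numbers describe the source of randomness, not the allocation scheme. Blocks, strata and minimisation can all use them, and central randomisation fits a restricted scheme. An article may leave such detail to a full protocol that is not shown, and likewise may leave covariates to an analysis plan. The text lists the effects to be assessed and does not say that covariates are excluded. On this view only one loose word remains.

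Much of this stands. A reader might infer that allocation is by independent coin toss, so that 40/40 would be unlikely. The document does not support that: it fixes 40 per arm, and a random permutation or blocks would give this every time. A reader might also infer that leaving out the factors biases the treatment comparison or makes the analysis wrong. It does not, because chance imbalance is already allowed for in an unadjusted test after randomisation, and balanced allocation makes that test conservative. Nor is the baseline comparison an error in itself, since the article does not use it to choose the analysis.

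What does not fall away is that the article itself asserts matching, names no method that yields it, and describes a model without the factors. That is a mismatch between stated parts, not an omitted detail. It bears on the between effect, which set the sample size with no margin.

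**Conclusion.** The point holds as an inconsistency with a cost in precision. The promise of matched arms has no stated mechanism, and the stated model does not use the factors.

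At 33 per arm, adjustment would raise power for the PASAT between effect from 0.80 to about 0.84, 0.88 or 0.92. If the arms are in fact balanced, the unadjusted test runs at about 0.039, 0.028 or 0.019 instead of 0.05, and the further gain in power from adjusting is smaller. These figures rest on assumed R² values of 0.1, 0.2 and 0.3 and on reading δ as the between-effect size, the reading that reproduces the plan's 33. Little or no gain should be expected for the time-by-treatment interaction. The allocation method actually used cannot be determined from the article.

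**What to change.** Before analysis, pre-specify age, sex, EDSS score and disease duration as fixed covariates in the primary model, whatever the p values in the baseline table. Add site if it was used in the allocation. State the allocation method actually used, including any balancing factors. If there was no balancing on the four factors, replace 'matched' with wording that describes randomised groups of equal size.

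The cost is a few sentences. Sex, age, EDSS score and disease duration are baseline items the plan already relies on, so no new data are needed. The model gives up 4 degrees of freedom, or 6 with three sites, out of 66 − 2 = 64. The sample size need not change on this account. The article's Timeline puts analysis after data collection ends in July 2026, so the model can be fixed even if enrolment has closed.
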